**Methods:**

In this RCT, 1200 English and Spanish-speaking CKD Stage 3–5 patients will be randomly assigned to one of two education conditions: *ET@Home* or KPSC standard of care education. Randomization will be stratified by CKD stage and primary language spoken. Those in the *ET@Home* condition will receive brochures, postcards, DVDs, and text messages delivering educational content in modules over a six-month period. Baseline data collection will measure demographics, transplant derailers, and the amount of previous CKD and transplant education they have received. Changes in CKD and transplant knowledge, ability to make an informed decision about transplant, and self-efficacy to pursue LDKT will be captured with surveys administered at baseline and at six months.

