**Fig. 1 Fig1:**
[figure not shown]
Patient Recruitment Flowchart

After completing the initial survey, enrolled participants will be randomized in a 1:1 ratio, stratified by race/ethnicity, language spoken, and CKD stage, to either the *ET@Home* intervention condition or standard KPSC education. The randomization sequence is produced electronically within the data capture system. Once an enrolled participant is assigned to an intervention arm, the study team will send the participant a notification of their assignment. Since this is an educational intervention, neither the study participants nor the study team are blinded to treatment assignment.

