### Statistical analysis

The available demographic and clinical characteristics of patients who refuse to join the study will be compared to those who enroll to determine if the patient selection procedure has resulted in a biased sample. A similar analysis will be conducted to compare the patients who fail to complete the six-month assessment. Multiple imputation by chained equations (MICE) will be used to multiply impute missing data. Imputation models will include all analysis and stratification variables. The intent-to-treat (ITT) approach will be applied in that all study participants will be analyzed according to the group that they were randomized to, regardless of whether they actually received their assigned intervention or not. Responses to the six-month intervention evaluation will be summarized for the sample overall and by levels of the stratification factors.

It is hypothesized that patients earlier in the CKD continuum, patients who speak Spanish, and non-White patients will have less knowledge about the opportunities for and risks and benefits of living kidney donation and will be making less-informed LDKT decisions. Investigators will evaluate these hypotheses using data from the pre-survey (baseline) by fitting multilevel random effects models with a random intercept to account for clustering at the CKD clinic level to compare differences in knowledge, informed decision-making, and Self-Efficacy. First, unadjusted models will be examined with the race/ethnicity, primary language spoken, and stage of CKD as independent variables for each test (separate models for each). Then, each of these models will be adjusted for other factors hypothesized to impact each outcome, including level of socioeconomic vulnerability, the level of previous transplant education received, the level of medical mistrust, and the level of health literacy. The addition of these variables will help test and control for confounding.

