Next, the effectiveness of *ET@Home* for CKD Stage 3–5 patients to increase LDKT knowledge and decision-making compared to KPSC education, by race/ethnicity and primary language spoken, will be evaluated. First, it will be determined if baseline differences in patient- and clinic-level variables are present using χ2 and Wilcoxon rank-sum tests, and subsequently adjustments for any out-of-balance characteristics in outcome analyses will be made. Differences in changes in transplant knowledge and Self-Efficacy using change scores, defined as the difference between the baseline and post-survey assessments, will be examined. Differences in these outcomes between the educational conditions will be tested using multilevel random effects models with normal outcome distributions, accounting for clustering with a random intercept for CKD clinic. Differences in informed decision-making will be examined using multilevel random effects logistic models. Finally, for the number of new steps taken, differences between the educational conditions in the count of new steps will be analyzed with a multilevel random effects Poisson model.

After the primary analyses are completed, multilevel random effects models will be constructed to examine the heterogeneity of treatment effect (HTE) using interaction terms for the *ET@Home* educational condition by the key patient subgroups by which randomization was stratified, including race, primary language spoken, and stage of CKD. For example, the *ET@Home* educational condition (*ET@Home* vs. SOC) x primary language (English vs. Spanish) interaction term will be tested, enabling us to determine of the *ET@Home* intervention was more or less effective for primarily Spanish-speaking patients than English-speaking patients.

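### Covariates for the randomised comparison are chosen by baseline significance tests, a rule that will almost never admit the stratification factors; the cost is efficiency and a data-driven model, not false positives

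*Protocol article*

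**What the plan says.** The rule is in the Protocol article, Statistical analysis, in the paragraph that opens the Aim 2 comparison. The opening step is a balance check: "First, it will be determined if baseline differences in patient- and clinic-level variables are present using χ2 and Wilcoxon rank-sum tests". The next step is that "subsequently adjustments for any out-of-balance characteristics in outcome analyses will be made". No list of variables and no threshold is given.

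The knowledge and self-efficacy outcomes are "change scores, defined as the difference between the baseline and post-survey assessments". They are compared in multilevel models "accounting for clustering with a random intercept for CKD clinic". Informed decision-making gets a multilevel logistic model and the count of new steps a multilevel Poisson model. No stratum term and no baseline outcome value is named for any of these.

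The strata are named elsewhere in the same section. For imputation: "Imputation models will include all analysis and stratification variables". For the later heterogeneity models, treatment is interacted with terms defined "by the key patient subgroups by which randomization was stratified". The one named adjustment set (socioeconomic vulnerability, previous education, mistrust, health literacy) belongs to the Aim 1 baseline models.

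On allocation, the section on eligibility, recruitment and randomization says "enrolled participants will be randomized in a 1:1 ratio, stratified by race/ethnicity, language spoken, and CKD stage". The abstract says "Randomization will be stratified by CKD stage and primary language spoken", without race/ethnicity.

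**The concern.** Any baseline difference between randomised arms is a chance difference. What makes a covariate worth adjusting for is its relation to the outcome, and a test between arms carries no information on that. The rule can therefore admit irrelevant variables and pass over useful ones, and the model behind the treatment estimate is settled only after data by arm have been seen.

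The rule also works against the stratification factors. Stratified allocation makes them nearly equal between arms, so a balance test has almost no chance of selecting them. Yet a factor that was balanced by design and also predicts the outcome is one that the model should contain; otherwise the reported standard error does not credit the balance. At stake are precision, and confidence that the primary model was fixed in advance.

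**Working it through.** **Inputs.** From Power analysis: difference 1.0 point, SD 4.0, two-sided alpha 0.05, 600 completers (300 per arm), stated power 0.90, standardised effect about 0.257 (0.25 in the next paragraph). Assumed, because the article gives no value: the number of baseline variables tested, the 5% threshold, and the share R² of change-score variance that the strata explain.

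**1. The plan's own figure.** Power = Φ(d/√(2/300) − 1.96), with √(2/300) = 0.08165.
- d = 0.257: Φ(3.148 − 1.960) = 0.883, close to the stated 0.90.
- d = 1.0/4.0 = 0.25: Φ(3.062 − 1.960) = 0.865.

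The calculations below start from 0.865 (difference 1.0, SD 4.0, SE = 4 × 0.08165 = 0.327).

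**2. How often chance picks a covariate.** With k independent tests at 5%, the chance of at least one flag is 1 − 0.95^k: 40% for k = 10, 54% for k = 15, 64% for k = 20.

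**3. Strata omitted after stratified allocation, exact balance.** The reported SE stays at 0.327, while the true SE is 0.327 × √(1 − R²).
- Reported/true SE = 1/√(1 − R²)
- Type I error = 2Φ(−1.96/√(1 − R²))
- Power, strata omitted = Φ((3.062 − 1.960)/√(1 − R²))
- Power, strata included = Φ(3.062/√(1 − R²) − 1.960)

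| R² | Reported/true SE | Type I error, omitted | Power, omitted | Power, included |
|---|---|---|---|---|
| 0 | 1.00 | 0.050 | 86.5% | 86.5% |
| 5% | 1.03 | 0.044 | 87.1% | 88.1% |
| 10% | 1.05 | 0.039 | 87.7% | 89.8% |
| 20% | 1.12 | 0.028 | 89.1% | 92.8% |

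**4. Attrition.** If half the patients are lost at random, about half of the stratified balance is lost among completers, so R² in the omitted-strata formulas becomes R²/2. The SE overstatement falls to 1.3%, 2.6% and 5.4% at R² of 5%, 10% and 20%. The power gap does not fall with it, because the precision that balance gave for free is lost too: omitted power becomes 86.8%, 87.1% and 87.7%. Included power stays close to the last column.

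**5. Simulation.** Settings: Table 3 cells, permuted blocks, 50% random retention, 10 independent covariates of which one explains 20% of variance, ordinary linear model without the clinic intercept, normal-theory baseline tests, 1,200 runs per scenario.
- At least one covariate was selected in about 40% of runs.
- A stratification factor was selected in 0 of 150 checked runs in every scenario.
- With strata explaining 10%, power was 0.85 unadjusted, 0.86 with test-based selection, 0.87 with strata, and 0.94 with strata plus the prognostic covariate pre-specified.
- Type I error under the test-based rule was 0.03 to 0.05.

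The largest gain thus comes from pre-specifying a covariate that predicts change. The baseline outcome value is the natural candidate. With equal SDs at both surveys and correlation ρ between them, adjusting for it leaves (1 + ρ)/2 of the change-score variance, so a 20% reduction corresponds to ρ = 0.6 (an assumption).

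**The case against.** The strongest reply is that the article nowhere says the strata are left out of the primary models. It names them for imputation and for the interaction models, and a full covariate list is something that an article may leave to the analysis plan. That stands: a reader might infer that the strata are excluded, and the document does not say so. What it does state is a rule for getting into the model, and balanced factors will rarely satisfy that rule.

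Four further limits also stand.
- A reader might infer that the standard errors ignore the design. They do not ignore clinics, which have a random intercept; only the stratification is in question.
- A reader might infer a risk of false positives. The error runs the other way: type I error is at or below 0.05, and test-based selection did not inflate it.
- The Aim 1 hypotheses predict lower baseline knowledge in certain groups. They concern level, whereas the knowledge analysis uses change, so they do not establish that the strata predict change. R² could be near zero, and then nothing is lost.
- The fair comparator is not a fixed 86.5%. If strata matter and allocation balances them, the unadjusted analysis already gains some power, so the gap in the table is about 1, 2 and 4 points.

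The disagreement over strata is minor. Table 3, Power analysis and Statistical analysis all agree with the main text in including race/ethnicity. Even without race strata, 200 patients allocated 1:1 would put 100 ± 14 in each arm (1.96 × √(200 × 0.25) = 13.9), an efficiency loss of about 2%.

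**Conclusion.** The point holds as a flaw in a stated rule. The article selects covariates for the randomised comparison by between-arm tests, which makes the model depend on chance and, in practice, keeps out the factors that the design balanced. The baseline outcome value has no stated place in it either.

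The size is modest. Under exact balance the overstatement of the SE is 3% to 12%, and the power forgone is about 1 to 4 points, for an assumed R² of 5% to 20%. With random 50% attrition the SE overstatement roughly halves, while the power gap is about 1 to 5 points. At R² = 0 there is no loss from omitting strata. The figures apply to the linear change-score models only and do not model multiple imputation or the clinic intercept. Validity in the sense of type I error is not threatened. The change is worth making because it is almost free, and because power at 1.0 point with SD 4.0 is 86.5%, below the stated 90%.

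**What to change.** - Delete the test-then-adjust step. Show baseline characteristics by arm descriptively, without p-values.
- Pre-specify one adjustment set for the Aim 2 models: the baseline value of the outcome, the five race/ethnicity-language groups of Table 3, and CKD stage. Keep the clinic random intercept. Any further prognostic covariate should be named now, from prior knowledge and not from balance between arms.
- For the logistic model of informed decision-making, state that the adjusted odds ratio is a conditional estimate. The SE factors above do not carry over to that model.
- Reconcile the abstract's strata with the randomization section, Power analysis and Statistical analysis. Confirm which factors the allocation system uses, since this decides which terms the model needs.

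The cost is analysis-plan wording and one sentence of the abstract. No additional data are needed, because the strata and the baseline outcomes are already collected. The change must be made before outcome data by arm are seen.

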#### Outcome measures and research methodology

In order to verify and demonstrate impact on improving knowledge of the process, risks, advantages, and disadvantages of deceased and living donation among dialysis patients, an RCT will be conducted. In this RCT, 1200 CKD patients in the KPSC system will be randomized to one of two education conditions (patient-guided *ET@Home* vs. standard KPSC transplant education, 600 patients per condition). Changes in key outcomes will be assessed comparing patient data collected at baseline and six months post-baseline. The primary outcome measures include patients’ knowledge of CKD and the risks and benefits of transplant and the capacity to make an informed decision about transplant. Additionally, key secondary measures will be examined, including self-efficacy to pursue DDKT and LDKT and steps taken towards transplant.

Comparisons in the two educational conditions’ effectiveness will also occur for patients earlier in the CKD continuum, patients who speak Spanish, and non-White patients.

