### Evaluation and statistical analysis plan

#### Power analysis

Based on the following assumptions, we estimated the sample size for the RCT. Using data from previous RCTs [4, 35], a mean knowledge change score of 1.0 points is estimated necessary to be detected among patients receiving *ET@Home* and standard KPSC education. Patients’ baseline transplant knowledge scores will be correlated with those of other patients from the same clinics [intraclass correlation coefficient (ICC) of 0.31]. The variance in knowledge change has both between- and within-cluster components, yielding a pooled standard deviation estimate of 4.0. Participant retention will be 50% at the 6-month assessment. Outcomes will be assessed using two-tailed statistical tests. Type 1 error rate (alpha level) will be set at 0.05. This study design will ensure power of 0.90. Power calculations for this trial are based on all of these factors, which yields a standardized effect size, accounting for clustering of approximately 0.257.

Power analyses based on changes in transplant knowledge, our primary study outcome, are presented. The study design and analyses were treated as a test of the difference between the mean knowledge score change of CKD patients in the *ET@Home* and standard KPSC education (control) conditions six months post-baseline. It is estimated that with 600 completed surveys (50% attrition), there will be a 90% power to detect a 0.25 effect size between two equal-sized groups (control and treatment groups). By stratifying recruitment and randomization by race/ethnicity (Asian, Black, Hispanic, White), primary language spoken (English vs. Spanish), and stage of CKD, according to the table below, this sample size will also have 90% power to detect 1 point differences in change on the transplant knowledge scale between the *ET@Home* and standard KPSC education conditions for these critical subgroups using interaction terms (e.g., treatment by race interaction, language by race interaction). Patients enrolled and randomized are shown in Table 3.

**Table 3 Tab3:** Patients enrolled and randomized

Race/Ethnicity/Language	Stage of CKD			
	3^a^	4	5/ESRD	Total
*English-speaking Asian*	67	67	66	200
*English-speaking Black*	67	66	67	200
*English-speaking White*	67	67	67	200
*English-speaking Hispanic*	67	67	66	200
*Spanish-speaking Hispanic*	133	133	134	400
Total	400	400	400	1200

^a^
*CKD* 3 patient recruitment prioritized based on likelihood to progress

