#### Informed decision-making

An informed decision-making measure was created from legacy measures and items generated from our formative work. Items for this scale were selected from legacy scales with good psychometric properties, like the Decisional Conflict Scale, whose total scale and subscales evidence high internal consistency, with Cronbach’s alphas ranging between 0.6–0.9. There was not a statistically significant difference between test-retest scores for this scale, and there was a high correlation (r = 0.80) between them [42]. Informed decision-making will be measured at baseline and six months.

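### Informed decision-making, a primary outcome built as a scale and measured twice, is given only a logistic model for its treatment comparison, with no stated use of its baseline value

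*Protocol article*

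**What the plan says.** All places are in the protocol article.

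- **Status.** Outcome measures and research methodology names two primary outcome measures: knowledge, and "the capacity to make an informed decision about transplant". The same section says: "Changes in key outcomes will be assessed comparing patient data collected at baseline and six months post-baseline". The Variables section also lists ability to make an informed decision among the outcomes that the post-survey measures in order to assess change.
- **Form of the measure.** The Informed decision-making section calls it a scale: "Items for this scale were selected from legacy scales with good psychometric properties". It adds: "Informed decision-making will be measured at baseline and six months". No score range, categories or cut-off are given.
- **Model.** Statistical analysis handles the first group of outcomes thus: "Differences in changes in transplant knowledge and Self-Efficacy using change scores, defined as the difference between the baseline and post-survey assessments, will be examined". Those outcomes get models with normal distributions. For the other primary outcome it says: "Differences in informed decision-making will be examined using multilevel random effects logistic models". All have a multilevel structure, with clinic as the cluster.
- **Baseline adjustment.** Baseline variables are first tested between arms, and "subsequently adjustments for any out-of-balance characteristics in outcome analyses will be made".
- **Hypothesis.** Aim 2, Hypothesis 1 is worded as a likelihood of making an informed treatment decision, not as a mean score.
- **Power.** "Power analyses based on changes in transplant knowledge, our primary study outcome, are presented". No power figure is given for informed decision-making.

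**The concern.** Three statements do not fit together without a further definition: the measure is a scale, its change from baseline is to be assessed, and its treatment comparison is logistic. A logistic model needs a binary or ordered-category outcome, and the article does not say how the scale becomes one.

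The contrast lies within one paragraph. Knowledge and self-efficacy refer to baseline through change scores, and steps do so by counting new ones. Informed decision-making alone has no reference to baseline. The imbalance rule does not fill the gap, because it brings in a baseline variable only when a test finds the arms different. The case for adjusting for the baseline value of an outcome is that it predicts the follow-up value, which holds whether or not the arms happen to differ.

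Precision on a primary outcome is at stake in a trial that plans for 50% retention and is powered on knowledge only. If the score is cut, the result also depends on where.

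**Working it through.** **1. The plan's own figure.** Power analysis states 90% power for an effect size of 0.25 with 600 completers (300 per arm), two-sided alpha 0.05. This concerns knowledge change.

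Power = Φ(d / √(2/n) − 1.96), with √(2/300) = 0.0816.
- d = 0.25: 0.25/0.0816 = 3.06; Φ(1.10) = 86.5%.
- d = 0.257 (the article's other value): 88.3%.

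So 90% is not quite reached at 0.25. That is a separate matter. Here 86.5% serves as the reference for an uncut score.

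**2. Inputs for informed decision-making.** From the article: 300 completers per arm, two-sided 0.05. Assumed, because the article gives no value: a normal score, a 0.25 SD shift (borrowed from knowledge), the cut point, and the baseline to six-month correlation. Clustering and imputation are ignored throughout.

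**3. Information kept by one cut.** With proportion q above the cut at c, efficiency relative to the uncut score is φ(c)² / [q(1−q)]. At the median: 0.3989² / 0.25 = 0.637, a loss of 36.3%. This is the best case.

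**4. Power after one cut.** The cut is placed so that q is the proportion above it midway between the arms. The two proportions are 1 − Φ(c ± 0.125), compared by a two-proportion test.

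| q above cut | Information lost | Proportions | Power |
|---|---|---|---|
| uncut | 0% | n/a | 86.5% |
| 50% | 36.3% | 45.0% vs 55.0% | 68.4% |
| 30% | 42.4% | 25.8% vs 34.5% | 64.0% |
| 20% | 51.0% | 16.7% vs 23.7% | 56.9% |
| 10% | 65.8% | 8.0% vs 12.4% | 42.9% |

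If q is instead the control-arm proportion, the 50%, 20% and 10% rows become 68.2%, 60.1% and 47.2%. The convention moves the off-median figures by 3 to 4 points and does not alter the pattern.

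**5. If the logistic model is ordinal.** With k equal categories of a normal score, the loss is about 21% (k = 3), 14% (k = 4), 10% (k = 5) and 4% (k = 10).

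**6. Value of the baseline score.** Adjusting the uncut six-month score for its baseline multiplies the residual variance by 1 − ρ².
- ρ = 0.3: factor 0.91, power 89.4%.
- ρ = 0.5: factor 0.75, power 94.2%.
- ρ = 0.7: factor 0.51, power 99.0%.

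The article quotes a test-retest correlation of 0.80 for a legacy scale. That suggests baseline will be prognostic but is not a six-month correlation for this measure.

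**The case against.** The strongest reply has four parts.

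**The loss of a third is conditional.** A reader might infer that the plan throws away at least a third of the outcome's information. The article does not support that. The figure needs a single binary cut and a near-normal score, and neither is stated. Logistic may mean ordinal, and the scoring may be in the full protocol or SAP. This stands, so the loss is given here only as a conditional figure.

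**Silence about baseline is not exclusion.** A reader might infer that the baseline value is never used. Two sections say change will be assessed, imbalance adjustment could bring the baseline score in, and a condensed article need not list covariates. This stands in part: the article does not rule baseline out. It does, however, state a method for using baseline with the neighbouring outcomes and a general rule that makes adjustment depend on a test. That rule is a stated choice, and for a primary outcome's own baseline value it is the weaker one.

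**The logistic model answers the hypothesis.** Hypothesis 1 concerns the likelihood of an informed decision, and a logistic model tests that directly. A mean score difference answers a somewhat different question. This stands, so the logistic model should not be called wrong or be replaced as a matter of course.

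**No stated power is contradicted.** The trial is sized on knowledge, and the 0.25 SD shift is borrowed. This also stands. Furthermore, logistic is the only model named for the treatment comparison, not for every use of the outcome: the Aim 1 and subgroup models are called multilevel without a stated distribution.

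**Conclusion.** The point holds in a limited form. The article describes this primary outcome as a scale measured twice with change to be assessed, yet names for its treatment comparison only a logistic model without a change or baseline term. As stated, its baseline value would enter only through a test for imbalance.

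The size is conditional. With one cut of a roughly normal score, the loss is at least 36%. For an assumed 0.25 SD shift and 300 completers per arm, that takes power from about 86% to 68% at the median and to between 43% and 47% at a 10% cut. An ordinal model would lose much less. Adjusting the uncut score for baseline would raise power to between 89% and 99% for correlations of 0.3 to 0.7. The shift, distribution, cut point and correlation are all assumptions, and clustering and imputation are left out.

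This is an inexpensive improvement in precision, not an error that invalidates the analysis.

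**What to change.** 1. Pre-specify that the six-month informed decision-making comparison always adjusts for the measure's baseline value and for the stratification factors, with the clinic random intercept, whatever the imbalance tests show.
2. Keep the logistic model to answer Hypothesis 1 as worded. State whether it is binary or ordinal and how the scale score maps to it, or refer to the document that does.
3. Add, as a pre-specified analysis, a linear mixed model of the uncut six-month score with the same adjustment. Whether it becomes the main analysis is the sponsor's choice. State that choice before the outcome data are seen.

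The cost is wording only, since both measurements are already planned. The one small drawback is that a mean difference is reported alongside the odds ratio, so the plan must say which carries the primary conclusion. If the measure is scored yes or no by design, one sentence saying so and baseline status as a covariate settle most of the point.

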Prospective participants who meet eligibility criteria will be sent an email inviting them to enroll in the study and asked to complete the initial transplant decision-making survey online or on the phone. Study staff will invite patients to participate in the RCT, beginning at the top of the risk-score ranked list, moving down the list until stratified cell targets are met. Recruitment will be stratified by race/ethnicity, language spoken, and CKD stage, oversampling smaller subgroups within the KPSC patient population. Expecting a response rate of 20%, an initial sample of 6000 patients will be invited to participate, resulting in a final sample of 1200 patients (Fig. 1). Clicking the survey link or contacting the study team by phone to begin the survey indicates consent to participate in the study. The email includes an opt out link if they do not wish to participate in the study. Invited prospective participants will receive follow-up invitations by secure email and phone to complete the initial transplant decision-making survey.

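### Table 3 nests language within ethnicity: the language by race interaction cannot be estimated, and the separately fitted Aim 1 contrasts partly mix language with ethnicity

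*Protocol article*

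**What the plan says.** All references are to the protocol article.

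- **Table 3 (Power analysis)** sets targets for five race/language cells. English-speaking Asian, Black and White patients have 200 each, "English-speaking Hispanic" patients have 200, and "Spanish-speaking Hispanic" patients have 400. There is no cell for non-Hispanic Spanish speakers.
- **Eligibility, recruitment, and randomization:** staff work through a risk-ranked list, "moving down the list until stratified cell targets are met". Participants are then "randomized in a 1:1 ratio, stratified by race/ethnicity, language spoken, and CKD stage".
- **Power analysis:** the sample is said to give 90% power for 1-point differences in the subgroups "using interaction terms (e.g., treatment by race interaction, language by race interaction").
- **Statistical analysis, Aim 1:** unadjusted baseline models are fitted "with the race/ethnicity, primary language spoken, and stage of CKD as independent variables for each test (separate models for each"). Each is then adjusted for further factors. Those named are socioeconomic vulnerability, previous transplant education, medical mistrust and health literacy.
- **Statistical analysis, heterogeneity of treatment effect (HTE):** interactions of treatment with race, language and CKD stage are planned. In the worked example, the ET@Home by "primary language (English vs. Spanish) interaction term will be tested".

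**The concern.** The trial wants conclusions by race/ethnicity and by language, at baseline (Aim 1) and for the treatment effect (Aim 2). The Table 3 targets tie the two factors together, since every Spanish speaker is Hispanic and most English speakers are not. This has two consequences.

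1. An interaction between language and race needs Spanish speakers in more than one race group. The design has them in one only, so the power section attaches a power figure to a term with no data behind it.
2. A model with language but not ethnicity compares an all-Hispanic group with a mostly non-Hispanic one. A model with ethnicity but not language compares a mostly Spanish-speaking Hispanic group with all-English groups. Either difference can be read as an effect of one factor when it belongs partly to the other. Whether a knowledge gap calls for better Spanish-language material or for something else depends on which factor it is.

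**Working it through.** **Inputs.** From Table 3 (printed row totals): English-speaking Asian, Black, White and Hispanic 200 each; Spanish-speaking Hispanic 400. From Power analysis: retention 50% (600 completers), SD of knowledge change 4.0, target difference 1.0 point, two-sided alpha 0.05, stated power 90%.

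**1. The plan's own power figure.** For the overall comparison with 300 completers per arm, power is 88.3% at effect size 0.257 and 86.5% at 0.25. The first is close to the stated 90%, the second less so. The 90% for interaction terms is not reproduced (step 4).

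**2. Can the language by race term be estimated?** Four race groups by two languages make 8 cells, of which 5 are filled.

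| Model | Columns | Rank |
|---|---|---|
| race + language | 5 | 5 |
| race + language + language × race | 8 | 5 |
| race + language, with treatment interactions | 10 | 10 |
| full, with treatment × language × race | 16 | 10 |

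Adding language × race brings 3 columns and no rank, so 0 of 3 terms are estimable. The three-way term with treatment is not estimable either. The additive model is estimable and has five parameters for five cells. It is therefore the five-level Table 3 factor in another coding: its language coefficient is Spanish- minus English-speaking Hispanic, and its Hispanic coefficient is English-speaking Hispanic minus White.

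**3. How much mixing occurs when the factors are fitted separately?**

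- Hispanic share: 400/400 = 1.00 of Spanish speakers and 200/800 = 0.25 of English speakers. Crude language contrast = language effect + (1.00 − 0.25) × Hispanic-versus-other effect, a weight of 0.75.
- Spanish-speaking share: 400/600 = 0.67 of Hispanic patients and 0 of White patients. Crude Hispanic-versus-White contrast = ethnicity effect + 0.67 × language effect.
- Non-White patients number 200 + 200 + 600 = 1000, so the non-White-versus-White contrast named in the hypotheses carries 400/1000 = 0.40 of any language effect.

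For the treatment interaction this was checked with 4000 simulated trials (600 completers, SD 4.0, treatment effect 1 point larger in Hispanic patients, no role for language). Treatment × language fitted alone averaged 0.75 point and was rejected in 18.8% of trials. With ethnicity and treatment × ethnicity in the model, it averaged 0.00 and was rejected in 5.3%.

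**4. What does separating the factors cost?** With 1:1 allocation, a treatment effect among n completers has variance 4·SD²/n. The interaction SE is then SD × √(4/n_A + 4/n_B), and power for 1 point is Φ(1/SE − 1.96).

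| Treatment interaction | Completers | SE | Power, 1 point |
|---|---|---|---|
| Language, whole sample | 400 vs 200 | 4√(4/400 + 4/200) = 0.69 | 30% |
| Language, within Hispanic | 100 vs 200 | 4√(4/100 + 4/200) = 0.98 | 17% |
| Hispanic vs White, all | 300 vs 100 | 4√(4/300 + 4/100) = 0.92 | 19% |
| Hispanic vs White, English speakers | 100 vs 100 | 4√(4/100 + 4/100) = 1.13 | 14% |

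No row is near 90%. The within-Hispanic language difference detectable with 90% power is about 3.2 points. These figures take SD 4.0 as given and allow no further loss for clustering.

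For the baseline contrasts in Aim 1 (all 1200 patients, equal variances, clustering ignored), the SE ratios are √[(1/400 + 1/200)/(1/400 + 1/800)] = 1.41 for language and √[(1/200 + 1/200)/(1/600 + 1/200)] = 1.22 for Hispanic versus White.

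**The case against.** Several points on the other side stand.

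- **The HTE text does not commit to separate models.** The instruction to use a separate model for each factor appears only for the unadjusted Aim 1 models. A reader might infer that the HTE analysis, as specified, will report an ethnicity effect as a language effect. The article does not say that, and joint fitting, which removes the mixing, is compatible with its wording.
- **The Aim 1 adjuster list is open-ended.** Race/ethnicity and language are not named, but they are not ruled out.
- **The crude contrast answers a legitimate question.** Whether the program works differently in Spanish- and English-speaking patients is a descriptive comparison, and the whole-sample difference is a true difference between those groups. Hypothesis 2 can also be read as a randomized comparison within each subgroup, which ethnicity cannot confound. The attribution problem weighs more on the adjusted Aim 1 models, which are said to control confounding.
- **The language by race term may be a slip** for treatment by language. It is one example in the power text, and the analysis section plans no such term. It still needs correcting, because a power figure is attached to it.

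A reader might also infer that no language effect can be estimated, or that leaving CKD stage out of these models confounds them too. Neither is supported. The 200 English-speaking Hispanic patients identify the language effect, and Table 3 spreads stage almost evenly within every cell. Nor do the eligibility criteria bar non-Hispanic Spanish speakers; the nesting comes from the cell targets.

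**Conclusion.** The point holds in limited form, at moderate severity. The language by race interaction cannot be estimated under Table 3. The Aim 1 race and language contrasts, fitted separately with only the named adjusters, mix the two factors with weights of 0.75 and 0.67. The HTE language contrast does the same only if treatment by language is fitted without treatment by race/ethnicity, which the article leaves unsaid.

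The weights assume that enrolment meets the Table 3 targets. The size in points depends on true differences that the documents do not give. A 1-point ethnicity difference would add 0.75 point to the language contrast, and a difference of 0.5 point would add 0.375. The primary overall comparison of ET@Home with standard education is unaffected, so this does not threaten the trial's main result.

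**What to change.** 1. **Power analysis:** delete the language by race interaction, or replace it with the treatment by language term of the analysis section. Do not attach the 90% figure to it.
2. **Adjusted Aim 1 models and HTE models:** fit race/ethnicity and language together, equivalently as the five-level Table 3 factor, with treatment interactions for HTE.
3. **Contrasts:** define the language effect as Spanish- versus English-speaking Hispanic patients, and take the race contrasts among English speakers.
4. **Reporting:** keep the crude whole-sample contrasts as descriptive subgroup results, labelled as not isolating language or ethnicity. This keeps a result for all Hispanic patients, since the separated Hispanic-versus-White contrast describes English speakers only.

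No new data and no change to recruitment are needed. The cost is precision, and the protocol should state it: with 600 completers and SD 4.0, the treatment by language SE rises from about 0.69 to 0.98 point and the Hispanic-versus-White interaction SE from about 0.92 to 1.13. Power for a 1-point within-Hispanic treatment by language difference is about 17%, so that result should be presented as an estimate with its interval rather than as a powered test.
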